### Study population

120 participants will be recruited from GGZ Drenthe, GGZ Friesland, GGZ Centraal, Lentis, UCP, Arkin and Dimence. Twenty-two participants per condition will be included in the fMRI part of the study. Onsite therapists will select the potentially eligible patients using seven screening questions.

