#### **4.1 Sample size calculation**

Sample size was calculated using the computerprogram SPSS Sample Power. In order to find a medium effect size (0.50) with two-sided  $\alpha=0.05$ , power=0.80 and taking 25% drop-out into account, 60 participants per group are needed. This means a total sample size of 120 participants.

Sample size in fMRI studies is usually not determined by power analyses, but by experiences with similar protocols. Exact power calculations are difficult because of the complex 'mass univariate' nature of brain imaging data as well as the difficulty to estimate effect sizes in different regions of interest beforehand. Previous studies suggest that in general, 20 participants are necessary per group to achieve sufficient power and acceptable reliability (Monti, 2011; Thirion et al., 2007). Therefore, in the fMRI-part of the proposed study, 22 participants will be included per group.

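### The inputs given for the sample size (d=0.50, two-sided alpha 0.05, 80% power, 25% drop-out) do not yield 60 participants per group

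*Protocol*

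**What the plan says.** The calculation is in the protocol, section 4.1 (Sample size calculation). It was done in SPSS Sample Power and opens with its target: "In order to find a medium effect size (0.50) with two-sided" alpha of 0.05. It then concludes: "power=0.80 and taking 25% drop-out into account, 60 participants per group are needed", for a total of 120. The Summary (Study population) repeats the total: "120 participants will be recruited from" the listed institutions.

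The section does not say which test was powered, at which visit, with how many measurements per person, or with what correlation between measurements.

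Three other places bear on the point:
- Section 8.2 plans a repeated measures ANOVA for long-term victimization, the primary outcome.
- Table 5 in section 6.3 schedules both victimization instruments (IVM and CTS2) at baseline and at four later assessments.
- Section 6.5 says that participants who withdraw are not replaced but are still invited to later assessments.

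**The concern.** An effect size, alpha, power and drop-out rate, with no test or correlation named, are normally read as a comparison of two group means. Read that way, 60 per group is too few even before the drop-out allowance is applied. Rounding or the choice of inflation formula cannot explain the gap.

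This is the only justification of the sample size for the main trial, since the fMRI part is argued separately. Readers will rely on the 80% when they interpret a null result. If it rests on an analysis gain that is not stated, they cannot judge whether that gain is plausible. If it does not, the figure is wrong.

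**Working it through.** **Inputs, all from section 4.1:** d = 0.50 (SD = 1); two-sided alpha = 0.05; power = 0.80; drop-out = 25%; equal groups; stated result 60 per group.

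**Step 1: try to reproduce 60.**

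Normal approximation: n = 2(1.960 + 0.842)² / 0.50² = 62.8, so 63 evaluable per group. The exact noncentral t calculation gives 63.8, so 64.

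| Variant | Evaluable per group | n/(1 − 0.25) | n × 1.25 |
|---|---|---|---|
| Two-sided, normal | 63 | 84 | 79 |
| Two-sided, exact t | 64 | 86 | 80 |
| One-sided, normal | 50 | 67 | 63 |
| One-sided, exact t | 51 | 68 | 64 |

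No variant returns 60. The one-sided rows conflict with the stated two-sided test, and the last column is an inflation that does not restore the required number. With the stated inputs, the two-sided exact t result is 64/0.75 = 85.3, so 86 per group and 172 in total.

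**Step 2: power at the stated size (exact t, one time point).**
- No drop-out, 60 per group: 77.5%.
- 25% drop-out, 60 × 0.75 = 45 per group: 65.0% (66.0% by the normal approximation).
- Effect detectable with 80% power at 45 per group: d = 0.597, about 0.60.

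**Step 3: could an unstated analysis gain close the gap?** The correlations below are assumptions; the protocol gives none.

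*One post-baseline measurement, adjusted for baseline.* The residual SD is √(1 − ρ²), so the effective d is 0.50/√(1 − ρ²). At 45 per group:

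| ρ (baseline–outcome) | Power |
|---|---|
| 0.30 | 69.1% |
| 0.50 | 77.3% |
| 0.55 | 80.2% |

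A correlation of about 0.55 is therefore needed.

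*Mean of the four post-baseline visits, not adjusted for baseline.* Assume a constant effect of 0.50 SD at every visit and the same correlation ρ between all visits. The variance of the mean is (1 + 3ρ)/4. At 45 per group:

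| ρ (between visits) | Variance of mean | Power |
|---|---|---|
| 0.3 | 0.475 | 93% |
| 0.5 | 0.625 | 84% |
| 0.6 | 0.700 | 80% |
| 0.7 | 0.775 | 76% |

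So 45 evaluable per group can reach 80% in some settings and not in others. Which one applies depends on inputs that section 4.1 does not state.

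**The case against.** The strongest reply is that a single-time-point t-test is not the planned analysis. Section 8.2 names a repeated measures ANOVA, Table 5 provides four post-baseline measurements, and the software may have been given a correlation that was left out of the text. Step 3 shows that such a calculation can exceed 80% with 45 per group.

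Much of this stands. A reader might infer that the trial's actual power is 65%, or that it has a one-in-three chance of missing a medium effect. The protocol does not support that: the 65% belongs to a two-group comparison at one time point, and section 4.1 names no test. Nor is a baseline correlation of about 0.55 a general condition for reaching 80%; it applies with one post-baseline measurement only.

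The reply does not rescue the sentence as written, because the inputs that might justify 60 are absent. They also cannot be taken for granted:
- The gain from averaging assumes a constant effect over time. The Summary (Objective) expects an effect on victimization to show only after a longer period.
- Section 6.1.2 sets the IVM recall window at five years at baseline, six months at the post assessments and one year at follow-up, so a high correlation between visits should not be presumed.

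It could also be said that actual loss may be below 25%, because those who withdraw are still invited. That is fair, but at one time point even zero loss leaves 77.5%.

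A reader might add that delivering the training in groups lowers power further. The protocol gives no intraclass correlation from which to put a figure on that, and it is not part of this arithmetic.

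**Conclusion.** The point holds as an error in a stated calculation: the inputs in section 4.1 do not produce 60 per group. For a two-group comparison of means at one time point, the requirement is 64 evaluable and about 86 recruited per group, against 60 recruited. At the stated size, power is 77.5% with no loss and 65% with 45 evaluable per group. These figures assume a t-test with equal groups and complete loss of the 25%.

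That the statement cannot be reproduced as written is firm. What the power of the planned analysis would be is open, because the test, the number of measurements and the correlation are not given.

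**What to change.** Keep N at 120 and correct the statement in section 4.1 in one of two ways.

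1. Restate it for a two-group comparison, for example: *Sixty participants per group, 45 evaluable after 25% drop-out, give 65% power for d = 0.50 and 80% power for d = 0.60 (two-sided alpha 0.05) for a comparison at a single time point.*
2. Base it on the planned repeated-measures analysis or on a baseline-adjusted one. Give the test and contrast that are powered, the number of measurements, the assumed correlation and the resulting power at 45 evaluable per group. If averaging over visits is used, say that a constant effect over time is assumed.

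If a correlation was entered in the software, the second option only requires reporting it. Either way the cost is a change of wording with no extra recruitment. Under the first option the stated power becomes less favourable.

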They will be instructed to hand in the device at the following appointment. Patients who are also interested in participating in the MRI sub-study and meet the additional MRI criteria, are asked for a pretest MRI session. During this appointment of approximately 90 minutes participants will perform two tasks in an MRI scanner. After the pretest(s), participants will either receive the psychomotor assertiveness training consisting of 20 weekly training sessions (treatment-group) or befriending sessions (control-group). The last session, participants again receive an accelerometer. They will be instructed to hand in the device at the post assessment. Within two weeks after the last intervention session, a posttest assessment will take place. The appointment will take approximately 180 minutes. With patients who also participate in the MRI sub-study, a posttest MRI session will be planned. After six months, participants will be contacted again for a follow-up assessment consisting of questionnaires similar to the earlier pre- and posttest assessment. Respectively, a year and two years later, participants will be contacted for a second and third follow-up assessment. These assessments will take approximately 110 minutes and consists of an interview and questionnaires. More details about the selection and pre- and posttest instruments can be found in paragraph 5.1. Table 5 shows the study design of the instruments (see appendix F for instruments). The selection assessment, pre- and posttest assessments, follow-up assessments with questionnaires and the intervention sessions will take place at the mental health care institutions. The MRI sub-study will take place at the Neuroimaging Centre in Groningen.

Table 5: study design of the instruments

| Instruments                                      | Pre-selection | Selection | Pre-assessment | Post-assessment | Follow-up I | Follow-up II | Follow-up III |
|---------------------------------------------------------|----------------------|------------------|-----------------------|------------------------|--------------------|---------------------|----------------------|
| Selection criteria evaluated by onsite therapist        | x                    |                  |                       |                        |                    |                     |                      |

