### 8.3 fMRI Analysis

The neuroimaging data will be analyzed using statistical parametric mapping 8 (SPM 8) (Wellcome Department of Cognitive Neurology London, UK; <http://www.fil.ion.ucl.ac.uk>). Preprocessing will include realignment, coregistration, spatial normalization into a standard space and smoothing. We will use traditional General Linear Model (GLM) voxel-wise analyses that will allow for the identification of threat-related brain activity. Baseline victimization scores as measured by the IVM (integrale veiligheidsmonitor) will be entered as regressors. Moreover, the effects of the training will be evaluated via 2 (Group: intervention, control) × 2 (Time: pre-, post intervention) interaction tests. Furthermore, we will study intrinsic connectivity during a resting state fMRI scan as a measure of brain system integrity. We will use region-of-interest (ROI) analyses for the amygdala to test our a priori hypotheses. The statistical thresholds we will employ are  $p < .05$  (smallvolume corrected) for ROI analyses and  $p < .001$  for whole-brain analyses.

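### Including 22 per group in the fMRI part leaves fewer than the 20 the protocol calls necessary for the pre-post test if more than 9.1% lack the second scan

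*Protocol*

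**What the plan says.** Protocol section 4.1 (Sample size calculation) sizes the two parts of the trial in consecutive paragraphs.

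- **Main trial.** The calculation ends with "taking 25% drop-out into account, 60 participants per group are needed". No time point is attached to the 25%, and no other drop-out rate appears in the protocol.
- **fMRI part.** The protocol explains that formal power analysis is difficult in imaging and relies on earlier studies suggesting that "20 participants are necessary per group to achieve sufficient power and acceptable reliability". It then draws the conclusion that "in the fMRI-part of the proposed study, 22 participants will be included per group". The Summary repeats the number: "Twenty-two participants per condition will be included in the fMRI part of the study". Neither place explains the margin of two or gives a loss rate for this part.

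Section 8.3 says that "the effects of the training will be evaluated via 2 (Group: intervention, control) × 2 (Time: pre-, post intervention) interaction tests". Section 6.3 puts the first scan before the 20 weekly sessions. On the end of treatment it says: "Within two weeks after the last intervention session, a posttest assessment will take place". A second MRI session is planned for sub-study participants at that stage. Section 6.5 rules out replacement of those who withdraw, but also says that they will be asked back for assessment after treatment and later.

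**The concern.** The fMRI number follows directly from a stated minimum, yet it carries almost no allowance for loss, while the paragraph before it allows for a quarter of participants to drop out. The training-effect test compares change between groups, and someone with only the first scan contributes no change. The 20 therefore has to be met by participants with two scans, not by participants included.

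At stake is the claim that the sub-study has adequate power and reliability for the training effect. That effect at the cerebral level is a stated objective (section 2), and the cerebral measures are listed among the mediators (Summary, main study parameters).

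**Working it through.** **Inputs**

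- Included per group: 22 (section 4.1 and Summary).
- Minimum per group: 20 (section 4.1).
- Drop-out: 25% (section 4.1, main trial, no time point). The protocol gives no rate for the fMRI part, so every other rate below is an assumption.
- Test: group by time, pre and post (section 8.3). No replacement (section 6.5).

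**Step 1. Can 22 be reproduced from 20?** The usual inflation is n / (1 − d). With d = 0.25 it gives 20 / 0.75 = 26.7, so 27. The cruder n × (1 + d) gives 20 × 1.25 = 25. Neither is 22.

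**Step 2. What loss does 22 cover?** Solving 22 × (1 − d) = 20 gives d = 1 − 20/22 = 2/22 = 9.1%.

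**Step 3. Expected number with both scans, 22 × (1 − d), and inclusion needed, 20 / (1 − d) rounded up**

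| Assumed loss by second scan | Expected per group from 22 | Inclusion per group needed to expect 20 |
|---|---|---|
| 5% | 20.9 | 22 |
| 10% | 19.8 | 23 |
| 15% | 18.7 | 24 |
| 20% | 17.6 | 25 |
| 25% | 16.5 | 27 |

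At 25% the shortfall is 20 − 16.5 = 3.5 per group, or 3.5/20 = 17.5% of the minimum.

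**Step 4. Chance of keeping at least 20.** If losses are independent, the number retained is binomial with n = 22.

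| Assumed loss | One group keeps at least 20 | Both groups do |
|---|---|---|
| 5% | 91% | 82% |
| 10% | 62% | 38% |
| 15% | 34% | 11% |
| 20% | 15% | 2.4% |
| 25% | 6% | 0.4% |

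The figures for both groups are the squares of the unrounded one-group figures.

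**The case against.** The strongest reply is that the 25% belongs to the main trial, whose primary outcome is long-term, and that it may describe loss by the last follow-up. The second scan comes after about five months. As an illustration, assume a constant rate of loss, so that retention at five months is 0.75^(5/T) when 25% is reached at month T.

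- If T is 29 to 35 months, loss by five months is about 4 to 5%, leaving about 21 per group.
- If T is about 11 months (the first follow-up), loss is about 12%, leaving about 19.
- If the whole 25% has occurred by the post-test, 16.5 remain.

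Constant loss is only an assumption, and early loss may be heavier. The reply stands to this extent: a reader might infer that 16 to 17 per group is what the trial will have, and the protocol does not support that as a forecast. It does not remove the point, because the protocol chooses none of these readings and any loss above 9.1% breaks its minimum.

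Three further replies limit the scope.

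- **Invitation after withdrawal.** Leaving the training does not automatically mean a lost second scan. Section 6.5 does not mention MRI, though, and an invitation does not guarantee attendance.
- **Nature of the 20.** It is a general rule from cited studies, and the protocol does not say whether it means completers or calls the extra two a drop-out allowance. A reader might infer a definite loss of power, but none can be derived from this document. The defect is a failure to secure its own minimum.
- **Other analyses.** A reader might conclude that the whole fMRI part is too small. The section 8.3 analysis with baseline victimization scores as regressors can use the first scans. Later drop-out does not touch those, and 22 exceeds 20 there.

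**Conclusion.** The point holds for the group-by-time fMRI test. Including 22 per group secures the stated minimum of 20 with both scans only if loss by the second scan is at most 9.1%, and the protocol neither states nor justifies such a rate. At its only stated rate, assumed to apply by the post-test scan, about 16.5 per group are expected. Over assumed losses of 5% to 25% the expected number runs from 20.9 down to 16.5, and of the rates tabulated only 5% meets the minimum. Unusable scans would add to the loss, but the protocol gives no figure for them and none is assumed here.

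The conclusion rests on reading the 20 as applying to participants who inform the pre-post contrast. The primary outcome is not affected.

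**What to change.** Restate the fMRI paragraph of section 4.1 to give the drop-out assumed by the post-test scan and the resulting expected number per group with both scans (about 16 to 17 if 25% is kept). Then do one of two things:

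1. justify a loss of 9% or less by that scan; or
2. state that the group-by-time fMRI test is expected to fall below the 20 per group considered necessary, and limit the power and reliability claim for that test accordingly.

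It would help to say in the same place whether the 20 means participants included or participants with both scans.

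The 27 in the working is not a proposal to add scans among people already enrolled. Participation in the fMRI part is a randomisation factor (section 6.2) and the first scan precedes treatment (section 6.3), so randomised participants cannot simply be added, and each addition would need two more MRI sessions.

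The restatement needs no new participants or scans. Its cost is a less favourable claim for the sub-study.

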In addition, we composed an advising committee of people who have both fighting sports experience and expertise in the field of psychiatry, psychology or psychomotor training. This committee critically reviewed the intervention protocols and provided feedback and suggestions for improvement.

The intervention consists of 20 weekly group training sessions of 75 minutes divided into five modules (see 4.1.1 for a description of the modules). Research shows that psychomotor therapy can have an effect on the mental health of patients with schizophrenia, if they have weekly sessions of one or two hours for three or six months (Marzolini, Jensen, & Melville, 2009; Scheewe et al., 2013), thus one session per week for five months should be sufficient to sort out an effect. Each session includes a warming-up, cooling-down, carry out the therapeutic martial arts exercises, and a group talk about the addressed themes (see 5.1.2 for the session procedure). The intervention has been evaluated and improved by means of a feasibility-study. Based on the feedback of participants as well as the trainers, the fighting expert and the researchers, some exercises have been adapted. For example, intensity, duration or techniques are changed in order to improve effectiveness.

The manual of the training and theoretical background information about the exercises and procedures are provided in appendix F2. All the sessions will be given by a psychomotor trainer and an expert by experience trained by the team that developed, gave and evaluated the training during the feasibility-study. The training consists of four sessions of 2,5 hours during which the most important exercises are trained and most important information is discussed. When the psychomotor assertiveness training has started, monthly supervision will be provided by the study investigators.

### **5.1.1 Modules**

#### **Module 1 Introduction**

In the first module the participants will be introduced to each other and learn more about the session procedures. The exercises and information focuses on self-stigma, safety, respect for each other, and how to establish and set boundaries. In addition, participants will monitor the tension level in their body, during and after exercises, and learn how to reduce tension. All exercises are done with the help of six basic kickboxing punches and kicks, and a basic fighting stance.

#### Module 2 Recognizing danger

The second module focuses on social cognition and insight. In addition to exercises from the first module that are repeated new exercises are offered regarding the recognition of emotion in facial expressions, prosody, and body language. Participants will learn the importance of considering other people's perspectives and how to verify their own. The techniques used in this module are blocking and deflection of the techniques learned in the first module. In addition, there are non-violent de-escalation techniques learned as an example of what a person could do in a threatening situation.

#### Module 3 How others see me

In the third module the participants will be practicing perspective taking To address this topic the participants will explore what kind of non-verbal signals they send out and find out how they react in threatening situations. Is their non-verbal reaction helpful or does it bring them in trouble? Furthermore, participants will learn how they can convincingly protect their boundaries and what signals to send out in threatening situations. The techniques used in this module are a combination of elements learned in the previous modules plus new basic kickboxing techniques.

#### Module 4 Aggression regulation

The focus of the fourth module is on aggression regulation. Ever since the first module the participant are paying attention to the tension in their body throughout each session. In this module participants will focus on anger and aggression: What are the bodily signals that their anger or stress is escalating and how does this affect their reactions to external stimuli? Participants will learn how to step back and reduce tension or stress. We will not introduce new kickboxing techniques but concentrate on the technique, power and speed of the ones already learned.

#### Module 5 Repeat and combine

In the fifth module exercises and topics from previous modules are combined and repeated when necessary. Furthermore, participants are stimulated to continue martial arts in a regular

sporting gym. A guest trainer from a local fighting school is invited to give a lesson of 30 minutes, making the step to a regular school more accessible for the participants.

### 5.1.2 Session procedure

There are 20 sessions of 75 minutes each. Table 1 shows the main program for each session. For a detailed description and background information about the program see appendix F2.

Table 1: session procedure

| Time in minutes | Program                               |
|-----------------|---------------------------------------|
| 10              | 1. Greeting ceremony and warming-up   |
| 30              | 2. Thematic exercises                 |
| 15              | 3. Repetition and extra exercises     |
| 10              | 4. Cooling-down and greeting ceremony |
| 10              | 5. Discussion                         |

